**Abstract**

**Background:** The human papillomavirus (HPV) is the most common sexually transmitted infection worldwide. The present study aims to examine the impact of an educational intervention based on the Health Belief Model (HBM) on sexual self-care among women of reproductive age infected with HPV.

**Method:** This is a randomized controlled trial with two parallel groups. Seventy women with HPV will be selected through simple random sampling from Arash Women's Comprehensive Hospital and Imam Khomeini Hospital in Tehran, Iran and will be allocated to a control group (n = 35) and an intervention group (n = 35). Participants in the intervention group will receive HBM-based sexual self-care education in four 45-60 min weekly sessions which will be held using the lectures, group discussions, question & answer sessions, PowerPoint presentations, pamphlets, educational videos, and role-playing. Data will be collected through a Demographic and obstetric information questionnaire, The Sexual Self-Care and HBM questionnaires, and will be analyzed through the ANOVA, Friedman test, and logistic regression modeling. All statistical analyses will be performed using SPSS version 24.

**Discussion:** Upon completion of this study, an increase in sexual self-care scores may indicate the effectiveness of this educational intervention. If proven effective, it can be recommended as a cost-effective method to achieve this goal, and it can be utilized by health professionals, including midwives and counselors to enhance sexual self-care among these women.

**Key-words:** Sexual Self-Care, Human Papillomavirus, Women, Health Belief Model, Intervention, Clinical trial

**Ethical code:** IR.TUMS.FNM.REC.1402.186

**Trial registration:** This study was registered in the Iranian Registry of Clinical Trials on 2024/01/01 (code: IRCT20231223060503N1)

**Plain English summary**

Human papillomavirus (HPV) is the most common sexually transmitted infection worldwide. Most HPV-related diseases are preventable through education, screening programs, and vaccination. However, many people lack sufficient information about prevention, screening, and self-care. This research will be an interventional study aimed at assessing the impact of an educational method on the sexual self-care of women with HPV. We will have two groups of women with HPV, each containing 35 participants. One group will participate in an educational program on sexual self-care, consisting of four sessions that include lectures, group discussions, Q&A sessions, PowerPoint presentations, pamphlets, educational videos, and role-playing. The other group will receive routine care. Finally, we will assess the effectiveness of the education on the sexual self-care of women with HPV.

**Background**

The human papillomavirus (HPV) is the most common sexually transmitted infection worldwide [1]. HPV strains are classified into low-risk and high-risk types based on their association with cancer [2]. The global prevalence of HPV is estimated to be 11.7%, with the highest rates observed in Southern Africa (17.4%), Eastern Africa (33.6%), Eastern Europe (21.4%), and Western Europe (9.0%) [3]. HPV transmission occurs through direct skin-to-skin or mucosal contact during vaginal, anal, or oral sex. Both asymptomatic and symptomatic individuals infected with HPV can transmit the virus [4]. However, most anogenital HPV infections resolve on their own; for example, over 90% of cervical infections clear within 1 to 3 years [5]. High-risk sexual behaviors, including a young age at first vaginal or oral intercourse and having more sexual partners, are the main risk factors associated with the acquisition and persistence of HPV infection and the development of related cancers. These sexual risk factors vary based on socioeconomic status, age, race, and education level [6,7]. It is estimated that around 2.8% of Iranian women in the general population have HPV16/18 infection. Iran has a population of about 33.5 million women aged 15 years and older at risk of developing cervical cancer, with 1,056 women diagnosed with cervical cancer and 644 deaths annually [8].

Most HPV-related diseases are preventable through education, screening programs, and vaccination [1]. HPV infection and genital warts have significant physical and psychological effects on women [9]. The more severe the disease, the greater the impact on mental health, which also imposes financial costs on healthcare systems [10]. A lack of awareness about safe sexual practices, the protective benefits of HPV vaccination, and the need for a range of tests could be the primary reasons for these issues [11].

Self-care refers to the ability of individuals, families, and communities to take intentional and purposeful actions to promote and maintain their health, prevent illness, and manage disease and disability, with or without the support of healthcare providers [12]. Effective techniques for enhancing self-care behaviors in women are organized into three categories: lifestyle modification, preventive behaviors and screening, and disease and treatment management behaviors. Self-care behaviors that help prevent HPV infection include undergoing Pap smears, vaccination, consistent and correct use of condoms during sexual intercourse, and limiting sexual partners to one [11,12]. Self-care interventions are among the most important and promising approaches to improving universal health coverage and well-being, both for health systems and individuals. As accessible, cost-effective, and acceptable interventions, they promote self-efficacy, independence, and participation in health [13], yet nearly four billion women of reproductive age worldwide lack access to such services [14].

One of the most widely used theories in health behavior is the Health Belief Model (HBM), which has extensive applications in health education for various health-related issues. The HBM posits that six constructs predict health behavior: perceived susceptibility, perceived severity, perceived benefits, perceived barriers, self-efficacy, and cues to action [15]. A study by Bayrami et al. (2019) aimed to assess the constructs of the HBM in relation to the willingness to receive HPV vaccination among female students at Urmia University of Medical Sciences. According to the results, perceived susceptibility, perceived severity, perceived benefits, perceived barriers, self-efficacy, and cues to action were all significantly associated with the acceptance of the HPV vaccine [16].

According to the results of a qualitative study conducted in Iran (2023), most women infected with HPV lacked sufficient knowledge about the virus, including its causes, symptoms, complications, prevention, and screening methods. Education, counseling, support, and healthcare services were identified as the main needs and challenges in reproductive and sexual health [17]. Based on the literature review, most studies have focused on the prevention of HPV infection. However, individuals who are already affected by this condition face numerous challenges, highlighting the need for further research into self-care practices for this group of patients. Given the Iranian and Islamic cultural context, HPV infection may be associated with negative psychological effects and significant challenges for Iranian women due to its sexual nature and the stigma attached to it, complicating efforts to educate, support, and address their needs [18,19]. Therefore, the present study aims to examine the impact of an educational intervention based on the Health Belief Model on sexual self-care among women of reproductive age infected with HPV.

**Hypothesis:** The educational intervention based on the Health Belief Model will lead to changes in perceived susceptibility, severity, benefits, barriers, and self-efficacy among women with HPV. These changes will, in turn, modify individual behavior and enhance sexual self-care in those affected by this disease.

**Objectives:** The primary objective of this study is to evaluate the effectiveness of an educational intervention based on the Health Belief Model on sexual self-care among women infected with the HPV. The secondary objectives of the study are:

1. To determine and compare the sexual self-care scores among women with HPV in the intervention and control groups before, immediately after, and 8 weeks following the intervention.
2. To determine and compare the items of the Health Belief Model (perceived susceptibility, perceived severity, perceived benefits, perceived barriers, cues to action, and self-efficacy) regarding sexual self-care among women with HPV in the intervention and control groups before, immediately after, and 8 weeks following the intervention.

**Method**

***Design***

This study will be conducted as a randomized clinical trial with one intervention group and one control group. The study aims to provide education based on the Health Belief Model to improve sexual self-care among women with HPV who attend the gynecology clinics of hospitals affiliated with Tehran University of Medical Sciences. This trial will follow the CONSORT guidelines (Figure 1) [20]. The current protocol has been structured according to the “Standard Protocol Items: Recommendations for Interventional Trials” (SPIRIT) checklist [21]. This study has been approved by the Ethics Committee of Tehran University of Medical Sciences with the ethics code (IR.TUMS.FNM.REC.1402.186) and has been registered as a clinical trial with the code IRCT20231223060503N1.

Figure 1. Participants’ flow in the study

## Follow-Up

Analysed (n= )
♦ Excluded from analysis (give reasons) (n= )

## Analysis

Analysed (n= )
♦ Excluded from analysis (give reasons) (n= )

Lost to follow-up (give reasons) (n= )

Discontinued intervention (give reasons) (n= )

Lost to follow-up (give reasons) (n= )

Discontinued intervention (give reasons) (n= )

## Enrollment

Allocated to intervention (n=35)

♦ Received allocated intervention (n= )

♦ Did not receive allocated intervention (give reasons) (n= )

## Allocation

Allocated to intervention (n=35)

♦ Received allocated intervention (n= )

♦ Did not receive allocated intervention (give reasons) (n= )

Randomized (n=70)

Excluded (n= )

♦  Not meeting inclusion criteria (n= )

♦  Declined to participate (n= )

♦  Other reasons (n= )

Assessed for eligibility (n= )

***Study population***

Study population consists of all women with HPV

***Study setting***

The setting of the study will be Arash Women's Comprehensive Hospital and Imam Khomeini Hospital. These clinics have been selected as referral hospitals in central and eastern Tehran, Iran.

***Participants***

Participants will be women with HPV who visit the women’s clinics at Arash and Imam Khomeini hospitals and meet the study inclusion criteria.

***Inclusion Criteria***

- - Positive HPV-DNA test
  - Iranian nationality
  - Married
  - Age between 15 and 49 years
  - Literacy (ability to read and write)
  - No chronic psychiatric disorders
  - No known malignant diseases
  - No previous participation in educational or counseling sessions related to STIs

***Exclusion Criteria***

- - Absence from more than two educational sessions
  - Incomplete or incorrect completion of the questionnaire
  - Lack of willingness to continue participating in the study

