***Sample Size***

To determine the necessary sample size, with a confidence level of 95%, a test power of 80%, and assuming that the effect size (Cohen's d) of the intervention compared to the control group is 0.7 [22,23], the minimum sample size required for each group is calculated to be 32 participants. Considering a 10% dropout rate, the sample size for each group will be set at 35 participants.

n = (2 × (z _(1-α/2)_ + z _(1-β)_))^2^ / (E × S)^2^ = (2 × (1.96 + 0.84))^2^ / (0.7)^2^ = 32

z _(0.975)_ = 1.96

z _(0.8)_ = 0.84

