**Table 1. Health Belief Model-Based Educational Intervention**

| **Session** | **Main Objective** | **Educational Content** | **Teaching Methods and Schedule** |
| --- | --- | --- | --- |
| First | Improve awareness about HPV and sexual self-care | PowerPoint presentation, Session 1 handout | 1) Introduction of the facilitator and participants, study objectives (10 min) 2) Information on HPV, its global and local prevalence, and the importance of sexual self-care (40 min) 3) Q&A session (10 min) |
| Second | Impact on perceived susceptibility, perceived severity, and perceived benefits of the Health Belief Model | PowerPoint presentation, Session 2 handout | 1) Review of the previous session (5 min) 2) Explanation of the consequences of not having a Pap smear test, non-vaccination against non-infecting strains, effects on marital life and quality of life, issues with having multiple sexual partners (45 min) 3) Q&A session to address perceived benefits (10 min) |
| Third | Impact on perceived barriers and self-efficacy of the Health Belief Model | PowerPoint presentation, Session 3 handout, Educational video | 1) Review of previous sessions (5 min) 2) Request women with HPV to share their issues since the onset of symptoms or diagnosis, discuss the concept of sexual self-care and its connection to self-efficacy (40 min) 3) Share common experiences and solutions with each other, summarize the taught materials using the educational video (15 min) 4) Q&A session (10 min) |
| Fourth | Impact on cues to action and performance of the Health Belief Model | PowerPoint presentation, Session 4 handout, Educational video, Role-playing | 1) Review of previous sessions (5 min) 2) Teach various sources of information about HPV (15 min) 3) Ask women to express their fears about symptoms and provide self-care recommendations, advise appropriate behaviors, and communicate problems and needs to healthcare providers (30 min) 4) Role-playing, educational video, and summarization of the taught materials (10 min) 5) Q&A session (10 min) |

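### Attendance is handled only after allocation, by a rule that can remove women from the intervention arm alone, and the sample size makes no allowance for partial attendance

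*Protocol*

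**What the plan says.** **Eligibility.** Protocol, Inclusion Criteria, lists eight items. The nearest to the subject is "No previous participation in educational or counseling sessions related to STIs", which concerns past education. None concerns ability to come to the classes. Sampling method says that the study procedures are explained and consent is obtained before allocation.

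**Attendance.** Protocol, Exclusion Criteria, gives "Absence from more than two educational sessions" as a reason for exclusion. With four sessions, a woman present at two is kept and a woman present at one or none is removed. The control group receives routine care and has no sessions.

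**Analysis set.** Data management and analysis states that every analysis is per protocol. No other set is named.

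**Content by session.** Table 1 gives session 2 the objective "Impact on perceived susceptibility, perceived severity, and perceived benefits of the Health Belief Model" and session 3 the objective "Impact on perceived barriers and self-efficacy of the Health Belief Model". Session 1 is about awareness, and session 4 about cues to action and performance.

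**Sample size.** The calculation is made "assuming that the effect size (Cohen's d) of the intervention compared to the control group is 0.7", at 95% confidence and 80% power. It finds that "the minimum sample size required for each group is calculated to be 32 participants", and then "Considering a 10% dropout rate, the sample size for each group will be set at 35 participants". No attendance rate is given.

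**The concern.** Two consequences follow from dealing with attendance only after the envelope has been opened.

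- **Bias.** The removal rule depends on behaviour after allocation and can operate in one arm only. Poor attenders are taken out of the intervention arm, while the control women who would have attended poorly cannot be identified and stay in. If poor attenders also differ in self-care, the comparison loses the protection of randomisation. The likely direction is in favour of the intervention, if women who keep coming are the more motivated ones.
- **Power.** Women who attended half the course are analysed as having followed the protocol. The threshold counts classes and ignores what each one teaches, so a woman who came to sessions 1 and 4 only is kept, although she missed both sessions whose stated objectives are the five constructs measured in Table 2. If partial attendance weakens the effect, 32 per arm has no reserve to absorb it.

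**Working it through.** **1. The plan's own figure.** Inputs from Sample Size: z = 1.96 and 0.84, d = 0.7.

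n per arm = 2 × (1.96 + 0.84)² / 0.7² = 2 × 7.84 / 0.49 = 32.0.

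The stated 32 reproduces. (As printed, the formula squares the 2 as well and would give 64; this looks like a misplaced bracket.) For dropout, 32 / 0.9 = 35.6, close to the 35 chosen, and 35 × 0.9 = 31.5 women remain per arm. The allowance is therefore used up by dropout.

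**2. Power with no dilution.** Two-sample t-test, two-sided 5%, d = 0.7: 78.7% with 32 per arm and 82.3% with 35.

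**3. Which attendance patterns are kept.** Four sessions give 16 patterns. At most two absences leaves 6 + 4 + 1 = 11. Of these, 4 include both sessions 2 and 3, and 1 (sessions 1 and 4) includes neither. The patterns are not equally likely, so the next step weights them.

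**4. Share of kept women who missed session 3.** The documents give no attendance rate. Assume that each session is attended independently with probability p.

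- Kept = 1 − (1 − p)⁴ − 4p(1 − p)³.
- Kept and missed session 3 = (1 − p) × [p³ + 3p²(1 − p)].
- p = 0.8: kept = 1 − 0.0016 − 0.0256 = 0.9728; missed session 3 = 0.2 × 0.896 = 0.1792; share f = 0.1792 / 0.9728 = 18.4%.
- p = 0.9: kept = 1 − 0.0001 − 0.0036 = 0.9963; missed session 3 = 0.1 × 0.972 = 0.0972; share f = 9.8%.

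**5. Diluted effect and power for barriers or self-efficacy.** Further assumptions: 0.7 is the effect in women who attended session 3, and women who missed it keep a fraction r of it. Then d = 0.7 × [1 − f(1 − r)].

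| p | r | d | Power, 32 per arm | Power, 35 per arm |
|---|---|---|---|---|
| 0.8 | 0 | 0.571 | 61% | 65% |
| 0.9 | 0 | 0.632 | 70% | 74% |
| 0.8 | 0.5 | 0.636 | 71% | 75% |
| 0.9 | 0.5 | 0.666 | 75% | 78% |

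**6. A cross-check that does not depend on session content.** If 20% of analysed intervention women half-attend and keep half the effect, d = 0.7 × (1 − 0.2 × 0.5) = 0.63. Power with 32 per arm is 69.9% by t-test (71.2% by normal approximation).

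**7. How many women the rule removes.** Under independence, 1 − 0.9728 = 2.7% at p = 0.8, or 0.027 × 35 ≈ 1 woman, and 0.4% at p = 0.9. Absences are more likely to cluster in women who stop coming, which would raise the number. The documents do not allow it to be estimated.

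**The case against.** **The benchmark is unknown.** A reader might infer that the contrast *is* diluted below 0.7 and that the stated power is simply wrong. The protocol does not support this. Sample Size attaches no attendance level to 0.7. An effect taken from an earlier educational study could already include missed classes, and then there is no loss. This stands in full, and the point is worded as a possibility for that reason.

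**Missing a session need not mean missing its content.** A reader of Table 1's objectives might conclude that the five constructs are taught in sessions 2 and 3 only. But sessions 3 and 4 open with a review, every session has a handout, and session 4 covers information sources and communication with providers, which bear on the self-efficacy items and on the barriers item about information. Zero carry-over is therefore the pessimistic end, and the rows with half retained are a reasonable counterweight.

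**The figures concern secondary outcomes.** The primary outcome is the 40-item FSHS score. Sessions 1 and 4 also carry self-care content, so no FSHS power figure can be derived from this model. This stands.

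**Women are told what is involved.** It would go too far to say that women are randomised without being asked about attendance. The procedures are explained before consent, and only volunteers are allocated. Still, explanation is not an eligibility requirement, and no criterion makes availability a condition.

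**Adherence thresholds belong in an SAP.** True of how a supportive adherence set is defined. The protocol itself, however, fixes a post-allocation removal rule together with per-protocol analysis throughout, and that combination is open to review here.

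**The two effects may offset each other.** One-arm removal could raise the estimate while partial attendance lowers it. The net direction is uncertain, but a bias of unknown size is no remedy for lost power.

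**Conclusion.** The point holds in limited form. The firm part needs no outside assumption: no criterion secures attendance before allocation, and the attendance rule can exclude women only from the intervention arm, so the per-protocol comparison is not the randomised one. How far this biases the result cannot be calculated from the protocol; with independent attendance of 80% or more, about one woman or fewer would be removed.

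The power part is conditional. Partial attendance has no allowance in the sample size, and 32 per arm has no slack. The losses in the table rest on three assumptions that the protocol neither states nor excludes: independent attendance of 80–90% per session, 0.7 as the effect under full attendance, and a retained effect of none or half. They apply to barriers and self-efficacy. Nothing here shows that the primary analysis has less than 80% power.

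**What to change.** 1. **Inclusion Criteria:** add a line such as *able to attend four consecutive weekly classes at the times offered*, asked of every woman before the envelope is opened so that it applies equally to both arms.
2. **Exclusion Criteria:** delete absence from more than two sessions as a reason for removal.
3. **Data management and analysis:** keep all randomised women, in the arm to which they were allocated, in the main analysis.
4. **Attendance:** record it session by session and use it only in a supportive analysis. Defining adherence by session content is an option there, not a requirement.

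**Cost.** The work is a short amendment and an attendance sheet. The population becomes slightly narrower, because women who cannot commit to the timetable are not enrolled. Deleting the removal rule on its own adds a little dilution: when all allocated women count, the share missing session 3 is 1 − p. With no effect retained and p = 0.8, d moves from 0.571 to 0.7 × 0.8 = 0.560, and power with 32 per arm from 61.4% to 59.7%. The case for deleting it is therefore the unbiased comparison and not power. The eligibility line is what should improve attendance, though its gain cannot be quantified from the protocol.

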***Sampling method***

After the study proposal is approved by the Ethics Committee of Tehran University of Medical Sciences, and after obtaining a Clinical Trial Registration Code (IRCT) and a written letter of introduction, eligible women will be enrolled in the study. Ethical conditions and considerations will be explained, and written informed consent will be obtained from those willing to participate. The researcher will first provide detailed information about the study, including its title, objectives, inclusion criteria, and the study's procedures. Participants will then be randomly assigned to either the intervention or control group using block randomization. Specifically, volunteers who agree to participate will be randomly allocated to the intervention or control groups using a block size of four. The educational intervention will be conducted in person. The intervention group will receive training based on the Health Belief Model, focusing on its constructs, in four sessions of 45-60 minutes each, held once a week with groups of 10-15 participants. This training will be provided by the researcher. The control group will receive routine care. The questionnaires will be administered to participants in both groups at three time points: before the intervention, immediately after, and 8 weeks post-intervention. To adhere to ethical considerations, the control group, if interested in receiving the training, will be provided with educational pamphlets and CDs after the intervention is completed. Figure 2 shows the schedule of enrolment, intervention, and assessment.

Figure 2. Schedule of enrolment, interventions, and assessments

|  | **STUDY PERIOD** | | | | | | | |  |
| --- | --- | --- | --- | --- | --- | --- | --- | --- | --- |
|  | **Enrolment** | **Allocation** | **Post-allocation** | | | | **Close-out** | |  |
| **TIMEPOINT**** | ***-t_1_*** | **0** | ***t_1_*** | ***t_2_*** | ***t_3_*** | ***t_4_*** | | ***t_5_*** | |
| **ENROLMENT:** |  |  |  |  |  |  | |  | |
| **Eligibility screen** | X |  |  |  |  |  | |  | |
| **Informed consent** | X |  |  |  |  |  | |  | |
| ***Randomized by independent person*** | X |  |  |  |  |  | |  | |
| **Allocation** |  | X |  |  |  |  | |  | |
| **INTERVENTIONS:** |  |  |  |  |  |  | |  | |
| ***Group A: educational intervention*** |  |  |  |  |  |  | |  | |
| ***Group B: control*** |  |  |  |  |  |  | |  | |
| **ASSESSMENTS:** |  |  |  |  |  |  | |  | |
| ***Demographic and obstetric information questionnaire*** | X |  |  |  |  |  | |  | |
| ***FSHS*** | X |  |  |  |  |  | | X | |
| ***Researcher-Designed Questionnaire Based on the HBM*** | X |  |  |  |  |  | | X | |

